#### Control group

The control group receives one structured psycho-oncological consultation (Control condition/Care as usual), which is regularly conducted by trained psycho-oncologists The duration of the consultation is approximately 30 min. Example issues discussed consist of the role of partner within the course of the illness including their own specific burdens and possibility of support. In addition they will receive a freely accessible booklet from the German Cancer Aid associated to their specific oncological disease.

#### Measures

Table 3 shows all study measures that are planned in the RCT. Demographic information such as age, sex, marital status, education, occupational situation in addition to treatment and disease related variables i. e. cancer diagnosis, date of diagnosis, past and current medical treatments, are collected using a standardized questionnaire.

The Depression module of the *Patient Health Questionnaire (PHQ-9)* is a valid self-report screening tool for depression. It consists of nine items each representing one criterion for major depression according to the Diagnostic and Statistical Manual of Mental Disorders, 4th Revision (DSM-IV). Items are scored on a four-point Likert scale from 0 (“not at all”) to 3 (“nearly every day”) with a total range from 0 to 27. Higher values indicate increased severity of symptoms. Scores > 9 indicate the presence of depression and further diagnostic assessment is recommended. Reliability and validity of the PHQ-9 is very good, and is preferably used compared to that of other screening instruments when evaluated with diagnostic criteria provided by the DSM-IV as a reference standard [23–25].

The *Generalized-Anxiety-Disorder-Questionnaire (GAD-7)* is a module of the Personal Health Questionnaire (PHQ) assessing generalized anxiety disorder. It consists of 7 items each of which reflect one DSM-IV criteria for generalized anxiety disorder. Items are scored on a four-point Likert scale from 0 (“not at all”) to 3 (“nearly every day”), resulting in a total range from 0 to 21. Scores from 0 to 4 denote an absence of anxiety while scores from 5 to 9, 10–15, and a score higher than 15 correspond to mild, moderate and severe levels of anxiety respectively. A cut-off value of ≥10 has been recommended to screen for any anxiety disorders. There is a high internal consistency of the German version of the questionnaire with Cronbach’s α =0.89. The German version has been validated and is commonly used in various diseases [22, 26].

The *Brief-Fatigue-Inventory (BFI)* is a short validated tool assessing the severity of fatigue in cancer patients and their partners. In the first step participants state whether they felt unusually tired or fatigued in the past week. In the second step 9 questions measure the experienced fatigue and its influence on aspects of the participants’ daily lives in the last 24 h. The BFI is rated on an eleven-point Likert scale ranging from 0 (“no fatigue”, “does not interfere”) to 10 (“as bad as you can imagine”/“completely interferes”). The mean BFI is calculated over the 9 questions with 1–4 indicating mild, 5–6 moderate, and 7–10 severe fatigue. The German version of the questionnaire shows a high internal consistency with Cronbach’s α = 0.92 [27].

The *Experience in Close Relationships scale (ECR-RD)* is a self-report questionnaire. It assesses patient and partner experiences in close romantic and non-romantic relationships and consists of two subscales: anxiety and avoidance. Items are scored on a seven-point Likert-scale ranging from 1 (“disagree”) to 7 (“agree”). Higher scores on one or both subscales indicate high attachment insecurity. Both subscales show high internal consistency with Cronbach’s α = 0.91 (anxiety) and α = 0.88 (avoidance) [28, 29].

The *Internality, Powerful others, and Chances scale (IPC)* assesses self and environment related cognitions on three dimensions: internality (conviction in having control over one’s own life), social related externality (having the impression of being dependent on other more powerful persons) and fatalistic externality (conviction that life is mainly influenced by fate/coincidence). It consists of 24 items which are scored on a six-point Likert-scale from 0 (“very wrong”) to 5 (“very correct”) [30].

The *Dyadic Coping Inventory (DCI)* is a self-administered instrument with 37 items which assesses stress and coping abilities within relationships when one partner is stressed. The DCI comprises four different dimensions/subscales: supportive DC e.g. ‘I show empathy and understanding’, delegated DC e.g. ‘I take on things that my partner would normally do in order to help him/her out’, negative DC e.g. ‘I blame my partner for not coping well enough with stress’, and stress communication e.g. ‘I let my partner know that I appreciate his/her practical support, advice or help’ as well as common DC e.g. ‘We try to deal with the problem together and look for concrete solutions’. It is also possible to assess the overall evaluation of DC which contains the satisfaction with DC and the evaluation of its efficacy. Each partner rates his own DC as well as the perceived DC of his partner. The items are rated on a five-point Likert scale from 1 (“very rarely”) to 5 (“very often”). The German version of the questionnaire shows a high internal consistency with Cronbach’s α = 0.91 [31–33].

The *Health Survey 12* (SF-12) is a general health questionnaire that assess health-related quality of life (QoL). It gives information about the health status of a person on eight different dimensions (physical functioning, physical role functioning, bodily pain, general health, vitality, social functioning, emotional role functioning and mental health). The dimensions can be summarized on two scales: the “mental health composite scale” and the “physical health composite scale”. The questionnaire consists of 12 self-administered items, which are rated on a 3, 5 or 6-point Likert scales. The two composite scales range from 0 very low Quality of Life (QoL) to 100 very high QoL. Most of the subscales show a high internal consistency with Cronbach’s α > 0.70 [33, 34].

#### Individual evaluation of therapy sessions

To evaluate each of the INPART group sessions we developed a specific questionnaire for each of the sessions asking to what extent the presented topic reflects the current concern of the partner and, at the same time, to what extend they perceived the therapy sessions helpful. An extra question aimed at the specific exercises of relaxation, resource activation and mindfulness in the session e.g., “To what extent could you get involved in the progressive muscle relaxation?”. For each of the evaluation questionnaires extra space is provided for individual feedback. We also developed a specific evaluation questionnaire for the therapists asking to what extent they felt to be supportive for the partners in respect to the relevant aspects.

#### Quality standards and therapist training

##### The INPART treatment manual

The INPART treatment manual was specifically developed. Until now there is no comparable group intervention program for partners of haemato-oncological patients available.

##### Therapist qualifications, INPART-training, and supervision

The INPART- courses are taught by professional psychotherapists and psycho-oncologists with specific psycho-oncological experience with at least two years of professional experience and a special certificate in psychosocial oncology. They will receive special training for the INPART program and will be supervised after each of the five sessions. The therapists of the control group will not receive any additional training but will also receive regular experienced supervision.

### Statistical methods

#### Power calculation

The sample size is determined based on a two-way ANOVA with two between-group factors (1: group, 2: centres) and a within-subject repeated measures factor (Time). Outcome criteria is the reduction of depression and anxiety (PHQ-9 and GAD-7). Alpha is defined with 0.05, Beta with 0.80. Effect size f (F-Test or ANOVA) is with 0.25 on an average level. Thus a sample size of *N* = 162 persons is necessary for finding a significant difference between intervention and control group (calculated with Gpower). The feasibility of the sample is based on the number of patients during 2016 in all three centres. According to the clinical cancer register there are 284 incidences per year in Leipzig, 292 in Hannover, and 372 in Ulm. Given an inquiry period of 27 months this would mean 639 patients in Leipzig, 657 in Hannover, and 837 in Ulm. Of these patients 25% will not fulfil the inclusion criteria (e.g. not living in a relationship, insufficient language skills) which means that 479 possible participants in Leipzig, 492 in Hannover, and 627 in Ulm can be addressed. After positive screening (50%) and acceptance of randomization (another 50%) there will be 119 participants in Leipzig, 123 in Hannover, and 156 in Ulm. The expected number of 4 intervention groups of 6 to 8 persons per centre can thus be easily achieved. The same number of groups / participants will be needed for the control group of the study.

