The program comprises of 5 weekly sessions lasting 1.5 h and additional home practice assignments. Groups consist of 6 to 8 participants. A presentation via Microsoft Powerpoint supports the structure of the course. In each session the participants receive material supporting the actual topic, a folder containing further information and home practice instructions for the forthcoming week. Table 2 shows the content of the INPART program per session.

**Table 2 Tab2:** Structure and content of the INPART sessions and home practice

Session	Content	Form of relaxation techniques
1	● Introduction to the course and goals of INPART	Progressive muscle relaxation (PMR)
	● Information about the specific burdens of partners of patients with cancer	
	● Identification and activation of resources	
2	● Identification of negative appraisals, interpretations and meanings ● Recognizing and down-scaling of excessive self-expectations to facilitate daily life	Guided imagery: encouragement of a benevolent companion
3	● Communication within relationship: Introduction to basic rules of successful communication, non-verbal communication, gender differences in communication	Autogenic training
4	● Dealing with emotions, (focus on anxiety)	Mindfulness-based stress reduction
	● Promotion of functional anxiety management	
	*Aim*: Reduction of dysfunctional coping and regain of control	
5	*Final session*: ● Coping in daily life	Guided Imagery: safe place
	● Outlook: taking next steps	
	● Reflection of the program	

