### Randomization procedure

Study entry requires a positive screening result and consent from the eligible partners. During screening partners are asked to fill out the PHQ-9 (depression) and the GAD-7 (anxiety). The necessary criteria for randomization is a cut-off score > 9 in at least one of the two scales (see [21, 22]). Randomization will be carried out on a basis of fixed blocks of flexible length. Within one block the assignment is balanced meaning that the number of interventions and control subjects are the same. The different length of the blocks is chosen to further reduce predictability of the assignment.

Possible selection effects will be documented to analyse their effect on the generalization of the results. Drop-out participants will be included in an intent-to-treat-analysis. To control for potential undesired side effects, other psycho-oncological or complementary interventions are recorded and considered in the analysis as well as information from the treatment process. In the case of events during the course of the study which may influence the therapeutic implications of the intervention negatively i.e. newly occurring exclusion criteria for example cognitive impairments or mobility deterioration, participants will be excluded. Psycho-oncological or psychiatric help is ensured by the local psychosomatic consultation-liaison and the psychiatric consultation services.

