#### Statistical analyses

In order to quantify the collected data descriptively summary statistics like mean values, variances, measures for value distribution and frequencies will be calculated for characteristics like frequencies of cancer types, gender, age and quality of relationship. For exploratory data analysis cross table evaluations will be performed including sociodemographic and disease specific control variables in order to find possible age or educational related effects. Correlation analyses will be used to assess the strength of associations between variables. At the interferential level mean comparisons via t-test or Mann-Whitney-U-Test will be employed to assess the efficacy of INPART in comparison to the control group at three different time intervals. We expect that that the level of depression and anxiety will change over time and a reduction is highest in the treatment group. Main analyses will be performed using a multivariate analysis of variance with repeated measures (MANOVA). In addition, multiple regression analysis will be applied to identify predicting factors (Table 4).

**Table 4 Tab4:** Descriptive and inferential statistics

Descriptive statistics	˗ Exploratory data analysis (value distribution, analyses of variance)
	˗ Cross table evaluation incl. Control variables (sociodemographic, disease specific)
	˗ Correlation analysis
Inferential statistics	˗ Comparisons of means (t-test or Mann-Whitney-U-test)
	˗ Multivariate analyses of variance (for multiple dependent variables), general linear model
	˗ (Multiple) logistic Regression for identification of predictors and determination of effectiveness
	˗ Actor-partner-interdependence model in order to investigate reciprocal influence within the dyad

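### Sample size and arm comparisons treat partners as independent although INPART is delivered in therapy groups; if outcomes correlate within groups, type I error can exceed 5%

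*Protocol article*

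**What the plan says.** All references are to the Protocol article.

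- **Delivery of INPART.** Under Intervention: "Groups consist of 6 to 8 participants". Power calculation expects four such groups at each of three centres. Table 1 makes therapist-led discussion among members a treatment component and intends partners to learn from one another.
- **Allocation.** Individual partners are randomised in balanced blocks (Randomization procedure): "Within one block the assignment is balanced meaning that the number of interventions and control subjects are the same".
- **Control.** Under Control group: "The control group receives one structured psycho-oncological consultation", lasting about 30 minutes.
- **Sample size.** The calculation is "based on a two-way ANOVA with two between-group factors (1: group, 2: centres", plus time within subjects. The first factor is the study arm, because the target is the number of "persons is necessary for finding a significant difference between intervention and control group (calculated with Gpower". The inputs are "Alpha is defined with 0.05, Beta with 0.80" (the second figure is evidently the power) and "Effect size f (F-Test or ANOVA) is with 0.25 on an average level". The result is 162.
- **Analysis.** Under Statistical analyses: "Main analyses will be performed using a multivariate analysis of variance with repeated measures (MANOVA", with t-tests or Mann-Whitney tests between arms. Table 4 adds regression and an actor-partner model for the couple.

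No therapy-group effect, therapist effect, ICC or design effect appears in the sample size or in the named analyses.

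**The concern.** Partners are randomised one by one, but those in the INPART arm are then treated together. Members of a therapy group share a therapist, a group atmosphere and each other's influence, which the programme uses deliberately. Their outcomes may therefore be more alike than those of partners in different groups. An ANOVA, t-test, Mann-Whitney test or MANOVA without a group term counts each partner as a separate piece of information.

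The centre factor does not solve this, because four groups sit inside each centre and can differ from one another. The actor-partner model handles correlation between patient and partner, not between partners in the same therapy group.

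At stake is the principal comparison: the standard error of the average effect would be understated, and the error would favour a claim of efficacy. The planned 162 carries no allowance for the same inflation.

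**Working it through.** **1. Reproduce 162.** Noncentral F test with noncentrality f²N = 0.0625·N, alpha 0.05, power 0.80, numerator df 2, six cells (2 arms × 3 centres). This gives N = 158, or 162 when rounded up to a multiple of six; power at 162 is 0.813. Repeated-measures versions also reach 162 under some settings (numerator df 5 with two occasions at correlation 0.5, or three at 0.6). Every route found to 162 assumes independent partners. The two-arm contrast alone (df 1) needs only 128, and 162 gives it 88.5% power under independence. That slack matters in step 4.

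**2. Cluster size.** 162/2 = 81 per arm; 3 × 4 = 12 therapy groups; 81/12 = 6.75 per group, inside the stated 6 to 8.

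**3. Inflation.** The ICC is an assumption, shown as a range. Clustering is taken in the INPART arm only, with equal total variance in both arms.

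- Design effect in the INPART arm: DE = 1 + (6.75 − 1)·ICC
- Variance inflation of the arm difference: V = (DE + 1)/2
- True standard error divided by the naive one: √V
- N carrying the information of 162 independent persons: 162·V, rounded up
- Approximate true type I error of a nominal 5% test: 2·[1 − Φ(1.96/√V)]

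For ICC 0.10: DE = 1 + 5.75 × 0.10 = 1.575; V = 2.575/2 = 1.2875; √V = 1.135; 162 × 1.2875 = 208.6, so 209; 1.96/1.135 = 1.727, so 8.4%.

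**4. Simulation at N = 162.** Three centres, four groups of 6 or 7 in each, 81 controls treated as singletons, one outcome per person, 40,000 runs. The naive test is the arm + centre ANOVA. The valid test compares therapy-group means with individual controls within centres, using Satterthwaite degrees of freedom. Type I ranges cover a repeat simulation. Power is for d = 0.5 (f = 0.25).

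| ICC | DE | V | √V | Equivalent N | Type I, formula | Type I, simulated | Power, valid test |
|---|---|---|---|---|---|---|---|
| 0 | 1.000 | 1.000 | 1.000 | 162 | 5.0% | 5.0% | 86.6% |
| 0.01 | 1.058 | 1.029 | 1.014 | 167 | 5.3% | 5.3–5.4% | 85.6% |
| 0.02 | 1.115 | 1.058 | 1.028 | 172 | 5.7% | 5.6–5.8% | 84.6% |
| 0.05 | 1.288 | 1.144 | 1.069 | 186 | 6.7% | 6.5–6.7% | 81.5% |
| 0.10 | 1.575 | 1.288 | 1.135 | 209 | 8.4% | 8.4–8.6% | 76.3% |
| 0.15 | 1.863 | 1.431 | 1.196 | 232 | 10.1% | 10.1–10.2% | 72.1% |

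In the repeat simulation power was within about one point of these values. The valid test held its level at about 5% throughout. Its 86.6% at ICC 0, against 88.5% for the naive test, is the cost of fewer degrees of freedom, not of correlation.

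**5. Sensitivity.** By the formula, groups of 6 and of 8 give 6.5% and 7.1% at ICC 0.05, and 8.0% and 9.2% at ICC 0.10. If controls were also seen in groups of this size with the same ICC, V would equal DE. At ICC 0.05 that is 1.288, the value shown for ICC 0.10 above, so about 8.4%.

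**The case against.** The strongest reply has four parts.

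1. **The excess is conditional.** The protocol gives no ICC. The programme is manualised with a fixed session structure, and therapists are trained and supervised after each session, all of which should limit differences between groups. Under a strict null, where attending a group changes nothing for anyone, individual randomisation protects the naive test. This stands: a reader might infer that the type I error does exceed 5%, but the document supports only that it can. What remains is that if groups differ in how well they work, the interval for the average effect is too narrow.
2. **Power.** A reader might infer that power must be below the stated 80%. The figures do not support that. Because 162 exceeds the 128 needed for the two-arm contrast, a valid test keeps about 82% at ICC 0.05; the shortfall appears at about 0.10.
3. **Controls.** A reader might take it as settled that controls are seen individually. The Control group section describes one consultation without saying so, Power calculation asks for as many groups or participants in the control arm as in the intervention arm, and the training section refers to control-group therapists. One-arm clustering is the more natural reading but is not stated.
4. **Detail for the analysis plan.** Degrees-of-freedom methods and identifier variables are commonly left to that document, and nothing shows that group membership goes unrecorded. This stands for those details. It does not cover the sample-size model and the main analysis, which this article states and which assume independence.

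**Conclusion.** The point holds in conditional form. The stated sample-size model and every named arm comparison treat partners as independent, while the INPART arm is treated in about 12 interacting groups; neither the centre factor nor the actor-partner model accounts for this.

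The consequence depends on an ICC that the document does not give. The excess type I error is nil at ICC 0, slight at 0.01 to 0.02, between one and two percentage points at 0.05, and takes the error to roughly 8.5% at 0.10 and 10% at 0.15. The nominal 80% power for f = 0.25 survives to about ICC 0.05 and not at 0.10.

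These figures assume 81 per arm, about 6.75 partners per group, clustering in the INPART arm only, equal total variances and one outcome per person. They do not simulate the full repeated-measures MANOVA, but that analysis as described has no therapy-group term either.

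**What to change.** - **Main model.** Replace the repeated-measures MANOVA as main analysis with a mixed model that keeps the repeated measurements within participant. Add a random intercept for therapy group in the INPART arm, centre as a fixed effect, and Satterthwaite or Kenward-Roger degrees of freedom.
- **Data.** Record therapy group and therapist for each participant as the trial runs.
- **Sample size.** Restate power at N = 162 over an ICC range such as 0.01 to 0.15, naming the contrast and the test used.
- **Control arm.** Reconcile the single consultation under Control group with the Power calculation sentence on the number of groups or participants needed for control. Treat controls as singletons only if they are seen individually; otherwise model clustering in that arm as well.

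The cost is a change of analysis wording and two identifier variables. The downside is slightly wider intervals and somewhat lower stated power: on the simulated figures, from 88.5% under independence to about 82% at ICC 0.05 or 76 to 77% at ICC 0.10.

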#### Statistical analyses

In order to quantify the collected data descriptively summary statistics like mean values, variances, measures for value distribution and frequencies will be calculated for characteristics like frequencies of cancer types, gender, age and quality of relationship. For exploratory data analysis cross table evaluations will be performed including sociodemographic and disease specific control variables in order to find possible age or educational related effects. Correlation analyses will be used to assess the strength of associations between variables. At the interferential level mean comparisons via t-test or Mann-Whitney-U-Test will be employed to assess the efficacy of INPART in comparison to the control group at three different time intervals. We expect that that the level of depression and anxiety will change over time and a reduction is highest in the treatment group. Main analyses will be performed using a multivariate analysis of variance with repeated measures (MANOVA). In addition, multiple regression analysis will be applied to identify predicting factors (Table 4).

**Table 4 Tab4:** Descriptive and inferential statistics

Descriptive statistics	˗ Exploratory data analysis (value distribution, analyses of variance)
	˗ Cross table evaluation incl. Control variables (sociodemographic, disease specific)
	˗ Correlation analysis
Inferential statistics	˗ Comparisons of means (t-test or Mann-Whitney-U-test)
	˗ Multivariate analyses of variance (for multiple dependent variables), general linear model
	˗ (Multiple) logistic Regression for identification of predictors and determination of effectiveness
	˗ Actor-partner-interdependence model in order to investigate reciprocal influence within the dyad

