## Abstract

**Background:**

Suffering from cancer confronts both the patient and their partner with a number of psychosocial challenges in various aspects of their life. These challenges may differentially impact on quality of life, coping ability and compliance to treatment. This especially holds true for haemato-oncological diseases. To date, psychological interventions have predominantly been developed for oncological patients however specific interventions for partners of haemato-oncological patients are rare. In this study we aim to conduct a psycho-oncological group-intervention for partners of patients with haemato-oncological diseases. The aim of the intervention is to significantly reduce symptoms of depression and anxiety in the partners and the patient, as well as enhancing dyadic coping.

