### Main study hypotheses

To alleviate depression as well as anxiety and to promote psychological well-being in partners of individuals with haemato-oncological disease the INPART-intervention was developed and will be tested in the proposed RCT. Principal hypothesis: A manualized group psychotherapy to treat clinically significant depressive and anxiety symptoms in partners of cancer patients with haemato-oncological disease will result in a greater reduction of depression and anxiety symptoms than in a control treatment of usual intervention (expected effect size ≥0,30) at three (t1) and six months (t2) after commencing intervention. In addition, the INPART program will lead to significant better DC. Secondary hypotheses: The INPART-intervention will result in better quality of life, better quality of the relationship and more self-efficacy than the control intervention. Between t1 and t2 a structured short-time psychotherapy in the intervention group will lead to further positive effects in the dependent variables compared to that of the treatment as usual group.

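### Unadjusted two-group tests at three times, one of them baseline, are assigned to assess efficacy, while the main MANOVA names no deciding effect and uses the baseline scores less efficiently than covariate adjustment

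*Protocol article*

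**What the plan says.** The Statistical analyses section assigns efficacy to two-group mean comparisons, by t-test or Mann-Whitney test, which are to "assess the efficacy of INPART in comparison to the control group at three different time intervals". No covariate is named. The Baseline assessment section lists the three data collections as baseline (t0), three months (t1) and six months (t2).

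The same Statistical analyses paragraph then gives the main analysis to a repeated-measures MANOVA and expects depression and anxiety to change over time, with the largest fall in the treated group. It does not say whether the group effect or the group-by-time effect decides. Table 4 lists the mean comparisons and the MANOVA, and adds logistic regression, partly to determine effectiveness.

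The Power calculation section assumes a "two-way ANOVA with two between-group factors (1: group, 2: centres) and a within-subject repeated measures factor (Time" and gives: "Alpha is defined with 0.05, Beta with 0.80"; "Effect size f (F-Test or ANOVA) is with 0.25 on an average level"; and a "sample size of *N* = 162 persons is necessary for finding a significant difference between intervention and control group".

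The status of the outcomes differs by section:
- Power calculation: "Outcome criteria is the reduction of depression and anxiety (PHQ-9 and GAD-7"), and nothing else.
- Main study hypotheses: partner depression and anxiety at t1 and t2 with an expected effect of at least 0.30. Then, ahead of the secondary hypotheses: "In addition, the INPART program will lead to significant better DC".
- Abstract, Background: the aim is to "significantly reduce symptoms of depression and anxiety in the partners and the patient", and to improve dyadic coping.
- Aims of INPART: distress and dyadic coping, in partners and patients.

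**The concern.** A comparison at t0 cannot bear on efficacy. It precedes treatment, and after randomisation any difference reflects chance. Listing it as an efficacy test is an error in the stated plan, and no further detail in an analysis plan would make it informative.

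At t1 and t2 the two-group tests ignore PHQ-9 and GAD-7 scores that every randomised partner is asked to provide at baseline. The MANOVA does use t0 if t0 is a level of its time factor. However, it treats the baseline score as a further outcome rather than as a covariate, and the article does not say which of its effects decides. That choice matters: a group effect averaged over t0, t1 and t2 dilutes any benefit with a visit at which none can exist.

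At stake is power that could be gained from data already collected, and a clear statement of which result answers the principal hypothesis.

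**Working it through.** **The plan's own figure.** N = 162 can be reproduced, although the article does not give the number of measurements or the correlation. With f = 0.25, alpha 0.05 and power 0.80 (the printed beta of 0.80 read as power):
- Repeated measures, between-subject effect, 6 cells (2 groups x 3 centres), 2 measurements and correlation 0.5 (the last two assumed): N = 160, which is 162 when rounded up to a multiple of 6.
- Fixed-effects ANOVA, 2 numerator degrees of freedom, 6 cells: N = 158, again 162 when rounded up.
- A plain two-group contrast would need 128.

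**Inputs for the comparison of analyses.**
- 81 per arm, from N = 162 and balanced blocks (Randomization procedure).
- d = 0.30, the lower bound in Main study hypotheses. The article does not state the metric, so reading it as a standardised mean difference is an assumption.
- d = 0.50, which is 2f for two equal groups with f = 0.25.
- Assumed: no dropout, the same true d at t1 and t2, equal variances, and a common correlation r between visits of 0.5 (range 0.3 to 0.7).
- Two-sided 0.05.

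**Effective standardised difference**, worked for d = 0.30 and r = 0.5:
- t-test at t1: d = 0.300.
- Group main effect over t0 to t2: (2/3)d / sqrt((1 + 2r)/3) = 0.200/0.816 = 0.245.
- Baseline-adjusted t1: d / sqrt(1 - r²) = 0.300/0.866 = 0.346.
- Baseline-adjusted mean of t1 and t2: d / sqrt((1 + r)/2 - r²) = 0.300/0.707 = 0.424.
- Group-by-time, 2 df: noncentrality (81/2)(2/3)d²/(1 - r) = 27 x 0.09/0.5 = 4.86, referred to F with 2 and 320 df.

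**Power**

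| Analysis | d = 0.30, r = 0.5 | d = 0.30, r = 0.3 to 0.7 | d = 0.50, r = 0.5 |
|---|---|---|---|
| Group main effect, t0 to t2 | 34% | 41 to 29% | 73% |
| Unadjusted t-test at t1 | 48% | 48% | 89% |
| Group-by-time, 2 df | 49% | 36 to 72% | 92% |
| Baseline-adjusted t1 | 59% | 51 to 76% | 96% |
| Baseline-adjusted mean of t1 and t2 | 76% | 72 to 89% | 99% |

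**Conditional error rate.** Suppose any one of four partner tests (PHQ-9 and GAD-7, at t1 and t2) could carry the claim at 0.05. If independent, the chance of at least one false positive is 1 - 0.95⁴ = 18.5%. By simulation it is about 14% with correlations of 0.7 between scales and 0.7 between times, and about 17% with 0.3 and 0.5. The range is therefore about 14 to 19%. If both scales had to succeed instead, alpha would not be inflated, but two independent outcomes at 0.80 power each give 0.80 x 0.80 = 0.64 jointly.

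**The case against.** The best defence is that the article does rank its methods. The MANOVA is the main analysis and the two-group tests only support it. The expectation stated beside it is a group-by-time pattern, so the fair comparator is the interaction test and not the diluted group main effect. This stands. At d = 0.50 and r = 0.5 the interaction test has 92% against 96% for baseline-adjusted t1, a small gap. A single-degree-of-freedom contrast of the follow-up mean against t0 does better still at d = 0.30: the effective difference is 0.300/sqrt(0.75 + 1 - 1) = 0.346, or 59% power. That is still below the 76% for covariate adjustment of the same mean. Repeated-measures analysis is also valid in a randomised trial, so the issue is efficiency and not bias.

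A reader might infer three stronger points, which the article does not support:
- That the plan discards its baseline data. This is true only of the two-group tests.
- That every outcome is tested at 0.05 with the overall error rate uncontrolled. Alpha appears once, for the sample size. No sentence says that one significant test is enough, and a multiplicity rule may sit in an analysis plan that is not shown.
- That a dozen tests, patient outcomes included, carry the principal claim. The principal hypothesis concerns symptoms in partners; patients come in through the abstract and the aims.

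None of this rescues the t0 comparison, names the deciding effect, or reconciles the sections on what is principal.

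**Conclusion.** The point holds in a limited form. One of the stated efficacy comparisons is at baseline and cannot show efficacy. The main analysis has no named deciding effect and uses the baseline scores less efficiently than it could.

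At d = 0.30 and r = 0.5, covariate adjustment raises power at t1 from 48% to 59%. It reaches 76% if the mean of t1 and t2 is the deciding contrast, against 49% for the 2-df group-by-time test. At d = 0.50 the gain is small. The 34% for a group main effect over all three visits shows why the deciding effect must be named; the article does not say that this effect decides. All these figures rest on an equal effect at both follow-ups, complete data and the assumed correlation.

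The sections also disagree on the status of dyadic coping and patient outcomes. The 14 to 19% false-positive range is a conditional note: it applies only under a rule that the article does not state, and is not an error in itself.

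**What to change.** - Make the main analysis a mixed model of t1 and t2 for each scale, adjusted for that scale's baseline score and for centre, and report the adjusted difference with its 95% confidence interval.
- State which contrast decides. The 76% belongs to the mean of t1 and t2; if t1 alone decides, the figure is 59%.
- Drop the t0 comparison as an efficacy test, and keep the t-tests and Mann-Whitney tests as description only.
- Reconcile the abstract, Aims of INPART, Main study hypotheses and Power calculation on whether dyadic coping and patient outcomes are principal or secondary.
- If the analysis plan does not already do so, state there whether PHQ-9 and GAD-7 must both succeed or either is enough, and control the error rate to match.

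The cost is wording, settled before outcome data are compared by arm. No participants, visits or questionnaires are added. The one consequence is that any outcome classed as secondary can no longer be claimed as a principal result.
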